#### **A multi-population approach predicts and explains motor recovery (HP1.4)**

The novel intensive HABIT-ILE therapy will be tested in two very different patient populations, namely infants with CP and adults in the chronic phase of stroke. Both populations will be imaged on the same scanner at St-Luc. The parameters of the diffusion gradients (duration, separation, intensity, waveform, orientation) and the distribution of these gradients across multiple "shells" (multi-shell HARDI) will be identical for both populations. This implies that any measured difference in DW-MRI signals arises solely from the WM tissue, which forms microstructural barriers to the diffusion of water. In other words, DW-MRI should provide a common scale to examine two seemingly different populations. The first tests on the new MRI scanner assisted by the GE-appointed MR physicist will determine whether the imaging parameters such as matrix and voxel size will be kept constant as well. At a fixed resolution, the motor tracts of infants will contain fewer voxels than those of adults given the overall size difference. Those tests will need to strike the right balance between sufficient resolution, signal-to-noise ratio and similarity between the two studies. In theory, microstructural indices derived from the advanced models described above are *not affected* by the voxel size because they provide indices that are averages over all the axons and cells of the voxel. At large voxel sizes however, several macro-environment may coexist and ultimately affect  $\mu S$  indices. Overall, we expect variables that are predictive for infants to be predictive for adults too, and conversely.

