Recent studies using animal models of CP demonstrate that this secondary damage is activity-dependent. Rodent studies have shown that motor-skill learning increases white matter DTI-derived fractional anisotropy (Brandão et al., 2018; Taub et al., 2004), suggesting that functional improvement of the CST is training-dependent (McKenzie et al., 2014; Xiao et al., 2016). In kittens, intensive motor skill training of the impaired forelimb in a specific developmental window of opportunity causes a rebalance in the CST synaptic projections to the spinal cord (Friel et al., 2012). In humans, the therapeutic window during which these projections might be rebalanced through motor stimulation has not been exactly identified. It is generally assumed to occur during early infancy, probably until the age of two (Martin & Lee, 1999), during the main period of axonal myelination in the CST (Li & Martin, 2000). In addition, transcranial magnetic stimulation (TMS) studies of motor-evoked potential in babies suggest that the CST system is organized during the first eighteen months of

life (Eyre et al., 2001), thus offering a therapeutic time window during which early stimulation may positively impact CST reorganization. Taken together these observations from animal and human studies suggest that early motor skill learning based interventions improve CST projections, thereby preventing secondary motor damage.

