## METHODS AND STUDY DESIGN

A randomized trial (RCT) is at the core of Grand Challenge 2, involving **48 infants** with CP between 6 and 18 months. Inclusion criteria will include: being diagnosed or considered at high risk of unilateral (RCT1) cerebral palsy, 6 to 18 months inclusive and ability to complete testing according to the age. Exclusion criteria will include epilepsy, botulinum toxin injections or orthopedic surgery within the past six months or during the study period, as well as severe visual and cognitive impairments preventing the child from being interested in simple games.

A pair-matched randomization will be used. Group allocation to either HABIT-ILE or a control condition will be randomly determined within each pair. As depicted in Figure 3, the HABIT-ILE group (n=24) will receive 50 hours of treatment over 2 weeks (5 h/day, 5 days/week) whereas the control group (unilateral n=24) will follow their usual activities for 2 weeks (nursery, ongoing therapy, generally a few hours of neurodevelopmental therapy per week, etc.). Usual activities have been chosen as control intervention since spontaneous activity of infants is oriented towards the discovery of their environment with motor activities in a nursery reaching around 5 hours per day. The between-group comparisons will be carried out between T0 and T+15 and between T0 and T+90. Participants in the control group will be offered HABIT-ILE training after assessment period 3. A supplementary assessment of this group at T0+180d will allow us to investigate the influence of the onset of therapy time and persistence of the therapeutic effects on the long term.

Each assessment will comprise clinical outcomes, biomechanical assessment, and neuroimaging outcomes (traditional and multi-shell HARDI DW-MRI).

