## CLINICAL STUDY DESIGN

[figure not shown]

Figure 5: design of the randomized controlled trial for a population of chronic stroke patients.

**Population:** N=48 (see sample size calculation). **Inclusion crit.:** being 1) a hemiparetic patient with a chronic stroke (>6 months), 2) 40-90 years old. **Exclusion crit.:** 1) alcohol/drug abuse, 2) pregnancy, 3) inability to understand/execute command, 4) major cognitive impairment interfering with the study (severe aphasia, psychiatric conditions), 5) uncontrolled health issues (cardiac/renal failure), 6) contraindications to MRI. In

order to span the largest possible range of neurological deficits, stroke of any type-size-location, involving either the dominant/non-dominant hemisphere will be included.

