## GRAND CHALLENGE 4: EXPLORING MECHANISMS OF TRAINING-INDUCED FUNCTIONAL RECOVERY THROUGH WM MICROSTRUCTURE IN VERY EARLY LESIONS VS ADULT ACQUIRED LESIONS

The identical experimental settings of WP 2 and 3 make it possible to directly compare WM baseline damage and training-induced changes between hemiplegic CP infants and adult stroke patients, both at the macroscopic level using whole-brain tractography and at the microscopic level using voxel-wise, model-based microstructural features. The deep underpinning of the differential repair mechanisms based on the initial conditions and age of the patients is likely to bring neurophysiological responses to the conditions allowing WM repair or training-induced changes. Investigating the best responders depending on initial conditions should help to better tailor treatment to each patient.

### RESEARCH HYPOTHESES OF GRAND CHALLENGE 4

Grand Challenge 4 will test the following hypotheses:

1. Experience-induced remodeling of the damaged CST occurs both in CP infants and adult stroke patients undergoing HABIT-ILE, but is stronger in developing CP infants **(HP4.1)**;
2. Neuroinflammation quantified by DW-MRI biomarkers is more predominant in developing CP infants compared to chronic adult stroke patients **(HP4.2)**.  
In both adult stroke patients and CP infants,
3. response to HABIT-ILE correlates *positively* with baseline DW-MRI markers quantifying the residual integrity of the damaged CST **(HP4.3)**;
4. response to HABIT-ILE correlates *negatively* with baseline DW-MRI markers quantifying a baseline enhancement of the ipsilateral, uncrossed CST **(HP4.4)**;
5. Combining DW-MRI  $\mu S$  markers of the CST with a whole-brain index of WM  $\mu S$  integrity correlates more closely with clinical response to HABIT-ILE than using exclusively the DW-MRI markers of the CST **(HP4.5)**.

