In a breakthrough exploratory step, we will try to combine functional and imaging data of CP infants and adult stroke patients using advanced model programming. Recovery in CP infants and stroke adults will be summarized and a normalization of the imaging data will be attempted for comparison in a common template. Whole-brain mapping of the two populations onto a common space may turn out to be too arduous due to very different brain sizes and large deformities in infants with CP. In that case, DW-MRI markers can always be compared after an adequate averaging over segmented sub-regions of the WM, such as the damaged or undamaged CST or regions not directly related to motor functions. Segmentation of the WM in the adult brain has become a routine task supported by many open-source software platforms. Improvements in the segmentation of the infant brain have also been gradually added to that existing software as well.

First, we hypothesize that, compared to baseline, HABIT-ILE intensive therapy induces remodeling of the  $\mu S$  indices of the damaged CST both in CP infants and adult stroke patients, but more so in developing CP infants **(HP4.1)**. The advantage of those DW-MRI indices is that their scale does not depend on brain size, brain age and are in theory only related to the morphology of the white matter independent of the imaging voxel size. If the hypothesis is verified (larger remodeling of the  $\mu S$  indexes in CP infants than in adult stroke patients), this would confirm potentially larger neuroplastic changes in the developing brain than in the aged brain, especially when combined with intensive rehabilitation, allowing for a lifespan quantification of neuroplastic potential. If the hypothesis is not verified, this would challenge the “classic” theory of larger neuroplastic potential in the developing brain.

Second, along the same line, we hypothesize that neuroinflammation quantified by DW-MRI biomarkers such as DIAMOND’s extra-axonal restricted diffusivity is more persistent in developing CP infants than in chronic

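### HP4.2 compares diffusion-MRI inflammation markers between infants and older adults with no age reference, so a maturational difference could mimic or mask the hypothesised effect

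*Protocol*

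**What the plan says.** The list of hypotheses in Grand Challenge 4 is introduced as hypotheses that will be tested. HP4.2 reads: "Neuroinflammation quantified by DW-MRI biomarkers is more predominant in developing CP infants compared to chronic adult stroke patients". The explanatory text below it puts the same hypothesis as: "neuroinflammation quantified by DW-MRI biomarkers such as DIAMOND’s extra-axonal restricted diffusivity is more persistent in developing CP infants than in chronic" adult stroke patients.

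The two populations come from separate trials. Infants enter Grand Challenge 2 on "being diagnosed or considered at high risk of unilateral (RCT1) cerebral palsy, 6 to 18 months inclusive" (Methods and study design). Adults enter Grand Challenge 3 with chronic stroke at "40-90 years old" (Clinical study design). Each trial plans 48 participants, all of them patients.

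Two statements support comparing the populations directly. In Grand Challenge 4, the paragraph on HP4.1, which the HP4.2 paragraph continues, says of the indices that "their scale does not depend on brain size, brain age and are in theory only related to the morphology of the white matter". In Grand Challenge 1, under HP1.4, identical diffusion gradients are said to imply that "any measured difference in DW-MRI signals arises solely from the WM tissue".

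**The concern.** The age ranges do not overlap, so a group difference in the marker is also an age difference. Covariate adjustment cannot separate the two; some form of reference is needed. The protocol attaches none to HP4.2 and relies on the indices being independent of brain age.

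At stake is what a positive result would mean. Read as the hypothesis is worded, a higher marker in infants would be taken as more neuroinflammation in cerebral palsy than in chronic stroke, when normal infant white matter might give the same picture. Equally, a maturational shift in the other direction could hide a real difference.

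A smaller matter is that HP4.2 speaks of predominance in one place and persistence in another. The first is a level, which one scan can show; the second suggests a course over time.

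**Working it through.** **1. Is there a figure to reproduce?** No. The protocol gives no sample size, effect size, SD or power for HP4.2. The sample-size calculations in Grand Challenges 2 and 3 concern hand-function scores within each trial.

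**2. The age-independence premise beside the rest of the protocol.**

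- Grand Challenge 1, the section on the quest for sensitivity and specificity, recommends DIAMOND for the infant study partly because in preterm infants it tracked microstructural maturation better than DTI. DIAMOND supplies the marker named for HP4.2.
- Grand Challenge 2, State of the art, places early infancy, probably to age two, "during the main period of axonal myelination in the CST".
- The HP4.2 rationale itself cites a study in which typically developing children show corticospinal integrity rising with maturation while children with unilateral cerebral palsy do not. That finding is interpretable because the study had a reference group. HP4.2 as written has none.

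A measurement scale may be the same at every age while normal values on it differ. The premise supports the first of these; HP4.2 would need the second to be false.

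**3. Acquisition.** HP1.4 fixes the same scanner and gradient scheme for both populations. It leaves matrix and voxel size to be settled by testing and accepts that large voxels can alter the indices. This is a secondary route to an offset.

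**4. What an offset would do (illustration).** Let d be an infant–adult difference, in SD units, due only to age or acquisition, with no difference in inflammation. The protocol gives no d, so the values are assumptions. Group sizes are 48 and 48, or 34 and 48, taking the success rate of at least 70% that the risk section gives for repeated infant MRI (0.70 × 48 = 33.6). Alpha is 0.05, assumed two-sided.

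SE = √(1/n₁ + 1/n₂), which is √(2/48) = 0.204 for 48 against 48 and √(1/34 + 1/48) = 0.224 for 34 against 48. Approximate rejection probability = Φ(d/SE − 1.96). For d = 0.5 and 48 against 48, Φ(2.449 − 1.960) = Φ(0.489) = 0.688; the exact t-test value is 0.679. Exact values:

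| Assumed d (SD) | 48 vs 48 | 34 vs 48 |
|---|---|---|
| 0 | 5% | 5% |
| 0.2 | 16% | 14% |
| 0.3 | 31% | 26% |
| 0.5 | 68% | 60% |
| 0.8 | 97% | 94% |
| 1.0 | 99.8% | 99% |

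**5. What referencing costs.** If each population is compared with m age-matched reference subjects of equal SD, SE = √(2/48 + 2/m). Relative to 0.204 this is a factor of 1.41 for m = 48 and 1.73 for m = 24 (both m assumed). The difference detectable with 80% power, (1.960 + 0.842) × SE, rises from 0.57 SD to 0.81 or 0.99 SD. An offset shared by patients and their references cancels.

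**The case against.** The other side has several fair points.

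- The statement that signal differences arise from tissue is not contradicted by myelination, since myelin is tissue. This stands. The difficulty is the further step from tissue to inflammation.
- Grand Challenge 1 describes DIAMOND's extra-axonal restricted fraction as highly specific to microglial activation, and nothing in the protocol says that this index moves with myelination. The maturation evidence is for DIAMOND in general, in preterm infants. This narrows the point without removing it: the risk section says that the biophysical specificity of these models was validated in animals, with less rigorous validation in humans, and the Introduction says that the biological meaning of such indices is still debated.
- No analysis model for HP4.2 is fixed. Left–right corticospinal ratios (HP1.3), averages over non-motor white matter (Grand Challenge 4) and external databases (WP3) are all mentioned, and an analysis plan not shown could use them. A reader might infer that the protocol commits to a raw comparison and excludes any reference. It does not; it only leaves them unconnected to HP4.2 while stating a premise under which they would seem unnecessary.
- Grand Challenge 4 calls combining the two populations exploratory, and no randomised comparison or primary outcome is affected. This limits the consequence, though the hypotheses are still put forward for testing.
- Predominance and persistence can both be read as a higher level in these patients. The wording point is minor.

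**Conclusion.** The point holds in limited form. Age and disease group are fully confounded in HP4.2, no age reference is tied to it, and the age-independence premise sits badly with the protocol's own account of DIAMOND and of corticospinal maturation. An unreferenced infant–adult difference cannot support a claim about inflammation in either direction.

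A reader might infer more: that normal maturation would be reported as excess inflammation in cerebral palsy. The documents do not support this, because they give no direction for the offset; an upward shift in infants would mimic HP4.2 and a downward one would mask it. Nor do they support treating 0.3 to 0.8 SD as expected offsets. Those figures show only how readily moderate offsets reach significance at this sample size. The 34-infant column is also pessimistic for a baseline comparison, since the 70% is a minimum for repeated scanning and baseline needs one scan. Acquisition is a lesser concern than age, given the shared scanner and gradients.

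**What to change.** - Qualify the age-independence sentence in Grand Challenge 4: a common measurement scale does not mean that normal values are equal in infants and adults.
- Report the unreferenced infant–adult difference as descriptive, not as evidence of more inflammation in cerebral palsy.
- Allow an inferential claim on HP4.2 only from age-specific Z-scores built on the DW-MRI databases in WP3, item 13, provided these cover both age ranges with compatible acquisition. The protocol does not say whether they do.
- Keep a within-subject regional contrast, such as damaged corticospinal tract against non-motor white matter, as a sensitivity analysis with its limits stated. The HP4.2 rationale allows for brain-wide inflammation after stroke, which could affect the reference region, and tract-specific maturation in infants need not cancel. The opposite corticospinal tract is not a clean reference either, because the same text reports reduced anisotropy in both tracts in unilateral cerebral palsy.
- Word HP4.2 in both places as a hypothesis about the level at baseline.

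The cost is wording and analysis only, with no new scans. Z-scoring adds some noise, more if the reference sample is small. If no compatible reference data are found, HP4.2 becomes descriptive.

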Compared to the animal literature, only a few motor intensive intervention trials have been carried out in very young children. To the best of our knowledge, these studies have all focused on children with unilateral CP and evaluated modified forms of constraint-induced movement therapy (CIMT), an intensive intervention performed sitting, requiring the physical immobilization (cast, glove,...) of the non-affected arm to promote the use of the affected arm (Deluca et al., 2012; Eliasson et al., 2011, 2018; Nordstrand et al., 2015; Taub et al., 2004). These studies have provided moderate support in favor of CIMT and suggested that higher daily intensity of training (Deluca et al., 2012; Taub et al., 2004) induced larger effects than lower daily intensity training (Eliasson et al., 2011, 2018; Nordstrand et al., 2015). CIMT focuses solely on the upper extremities of children with unilateral CP (Deluca et al., 2012; Eliasson et al., 2011, 2018; Nordstrand et al., 2015; Taub et al., 2004), despite the fact that the lower extremities are also commonly affected. Moreover, none of these studies has investigated the possible impact of these interventions on myelination, organization and projections of the CST, which may be accessed using advanced analyses of DW-MRI acquisitions.

## RESEARCH HYPOTHESES OF GRAND CHALLENGE 2

In Grand Challenge 2, we will specifically target this secondary damage in infants with CP, aged 6 to 18 months, by demonstrating **for the first time** that it might be **prevented** by an intensive treatment program, the 'Hand-arm-bimanual-intensive-therapy including lower extremities' (HABIT-ILE). We will investigate therapeutic outcome through a multimodal analysis of neuroplastic changes (see Grand Challenge 1), a thorough assessment of motor function and activities outcomes. This will also advance our understanding of motor control changes through muscles activation and kinematic assessment. Targeting the secondary damage will in turn prevent part of the motor disability and thus improve functional abilities and motor control. For the first time, a large-scale study will be conducted to test this hypothesis in young children with unilateral CP.

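### HP4.1 compares change from baseline in treated infants and treated adults without the control arms, so spontaneous infant change may be read as greater training-induced plasticity

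*Protocol*

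**What the plan says.** In the protocol's Research Hypotheses of Grand Challenge 4, HP4.1 reads: "Experience-induced remodeling of the damaged CST occurs both in CP infants and adult stroke patients undergoing HABIT-ILE, but is stronger in developing CP infants". The explanatory text sets the comparator: "First, we hypothesize that, compared to baseline, HABIT-ILE intensive therapy induces remodeling of the" microstructural indices of the damaged CST, with a parenthesis that repeats only the infants-above-adults part. It then fixes the reading. If infants change more, "this would confirm potentially larger neuroplastic changes in the developing brain than in the aged brain"; if not, the usual theory of greater plasticity in the developing brain would be challenged. The ground given for comparing across ages is that, for these indices, "their scale does not depend on brain size, brain age".

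Other sections bear on this. Research Hypotheses of Grand Challenge 2 enrols "infants with CP, aged 6 to 18 months". The State of the Art of Grand Challenge 2 puts the window for rebalancing CST projections in early infancy, "probably until the age of two", "during the main period of axonal myelination in the CST". Item 2 of Grand Challenges of the Research also describes connectivity under two years as developing especially actively. In the other direction, the discussion of HP4.2 cites a study in which children with unilateral CP showed no maturational rise in CST integrity.

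Both trials randomise a control arm, image it at T0, T0+15 and T0+90 days, and offer it HABIT-ILE only after the third assessment.

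**The concern.** Change from baseline in a treated group is the training effect plus whatever would have happened without training. In adults more than six months after stroke the second part may be close to zero. In infants of 6 to 18 months it may not be. Comparing the two treated groups therefore mixes a difference in training effect with a difference in spontaneous change.

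The statement about scale does not help. It says that a unit of the index means the same thing at any age. Growth alters the tissue itself, and a perfectly comparable index would record that alteration faithfully.

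At stake is the cross-population conclusion. The protocol commits itself in advance to interpreting a larger infant change as larger neuroplastic change, in a section that calls the remodeling experience-induced. The control arms could separate growth from training, but the stated contrast leaves them out.

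**Working it through.** **Figures in the plan.** HP4.1 has no sample size, SD, alpha or power of its own. The arm size of 24 comes from the two clinical calculations. Two-sided 0.05 and 90% power give n = 2 × (1.960 + 1.282)² / d². For infants, d = 7.2/5.9 = 1.22 and n = 15, as stated. For adults, d = 6/5 = 1.20; the normal formula gives 15 and the t-based value is 15.6, hence the stated 16. Both trials then enrol 24 per arm.

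**What the stated contrast estimates.** Let τ be the true training effect and m the spontaneous infant change, with none in adults.

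- Treated infants minus treated adults: (τ_infant + m) − τ_adult = (τ_infant − τ_adult) + m.
- Difference of the two randomised differences: (τ_infant + m − m) − (τ_adult − 0) = τ_infant − τ_adult.

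The first is biased by m; the second is not.

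**Assumptions not in the documents.** SD of change is 1 in every arm, τ is equal in both populations, and m ranges from 0 to 1 SD.

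**Chance of a significant result favouring infants** (t test, two-sided 0.05). The noncentrality is m / √(1/n₁ + 1/n₂). With 24 and 24 the standard error is √(2/24) = 0.289, so m = 0.5 gives 0.5/0.289 = 1.73 and a probability of 0.40. The protocol's high-risk section expects repeated infant MRI to succeed in at least 70%, and 0.7 × 24 is about 17. With 17 infants and 24 adults the standard error is √(1/17 + 1/24) = 0.317.

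| Assumed m (SD) | 24 infants, 24 adults | 17 infants, 24 adults |
|---|---|---|
| 0 | 2.5% | 2.5% |
| 0.25 | 13% | 12% |
| 0.5 | 40% | 34% |
| 0.75 | 72% | 64% |
| 1.0 | 92% | 87% |

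The reference rate is 2.5%, because only one direction supports the hypothesis.

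**Both parts of HP4.1 together.** The numbered hypothesis also requires remodeling in adults. With no therapy effect anywhere and stable adults, requiring a significant adult change in the same direction as well as infants above adults is met by simulation in only about 0.05 to 1.2% of cases for m from 0.5 to 1.0 SD.

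**The interaction instead.** Simulated two-sided error stays at 4.9 to 5.1% for m from 0 to 1 SD. The standard error is √(4/24) = 0.408, which is 1.41 times 0.289. With 17 infants per arm and 24 adults it is √(2/17 + 2/24) = 0.448. The detectable difference at 90% power is 3.242 × 0.408 = 1.32 SD, or 3.242 × 0.448 = 1.45 SD.

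**The case against.** The case on the other side has five parts.

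- **Spontaneous change is not established.** HP4.1 concerns the damaged CST, and the protocol's own citation in unilateral CP found no maturational increase. The myelination passage is hedged and gives no rate over 15 or 90 days. This stands: a reader might infer that growth will certainly be taken for plasticity, and the documents do not support that. But the citation is used for HP4.2, not to justify leaving controls out, and it conflicts with the other passages. That is a reason to measure the change.
- **HP4.1 has two parts.** A reader might infer that it would be confirmed even if HABIT-ILE did nothing in either population. As numbered, it would rarely be met in that case, because adults would show no remodeling. This stands. The bias matters mainly when therapy works in both populations, or when only the parenthesis is tested.
- **No test or model is fixed, and a SAP may add control adjustment.** This is partly right, since a baseline comparison does not rule adjustment out. But the protocol names the comparator and the interpretation, and a SAP that follows them faithfully would produce the biased contrast. The between-group analyses in Grand Challenges 2 and 3 each stay within one trial.
- **The promised reading is hedged and could mean plasticity of the developing brain in general.** Yet the hypothesis is labelled experience-induced, and growth alone would not test it.
- **The work is exploratory.** It is, and this limits the severity.

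A reader might also infer that delayed-phase data are to be pooled for HP4.1. No text proposes that; the remark about a larger group concerns adult HABIT-ILE data generally.

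**Conclusion.** The stated contrast is biased by any spontaneous infant change, and the randomised data that would remove the bias are left unused. The size depends on an unknown: with equal therapy effects and assumed drift of 0.25 to 1.0 SD, the stronger-in-infants part is falsely significant in about 13 to 92% of cases at 24 per group, or 12 to 87% with 17 infants and 24 adults. With no drift there is no bias. Drift has more time to accumulate by T0+90 than by T0+15 days.

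The consequence is limited to the cross-population conclusion. The randomised comparisons within each trial, the primary outcomes, the sample sizes and the data collection are unaffected. This should be fixed, but it does not threaten the trials themselves.

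**What to change.** Define the between-population part of HP4.1 as the population-by-arm interaction on change in the CST indices: (HABIT-ILE minus control change in infants) minus (HABIT-ILE minus control change in adults). Take it over T0 to T0+15 and T0 to T0+90 days, before the controls receive HABIT-ILE. Reword the interpretive sentences to refer to this quantity, and present it as exploratory.

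No new patients or scans are needed. The cost is precision: the standard error rises from 0.29 to 0.41 SD at 24 per arm, or to about 0.45 SD with 17 infants per arm. Only differences of about 1.3 SD or more are then detectable with 90% power, which is above the roughly 1.2 SD clinical effects used to size the trials. The protocol should say so, and should add that a non-significant interaction is not evidence of equal plasticity.

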- 4) The HABIT-ILE intervention *per se* will require the participation and motivation of participants for many hours per day. This represents a potential high risk of either not meeting the high-intensity goals set in the HABIT-ILE therapy (e.g. due to lack of motivation leading to a small amount of repetitions) or of complete drop-out, both in infants and in adults who will mainly be up to 70 years of age.

Circumventing those limitations may be done via the following:

- 1) While cortical segmentation and white matter streamlines clustering should proceed fairly seamlessly in adult stroke patients, those tasks may prove more arduous in infant brains. In the worst case, segmentation will need to be performed manually based on anatomical landmarks for all 48 subjects of the CP study. However, the most likely scenario is a semi-automated framework where seeds would need to be manually placed at sites visually located on the MR images and automatic tractography would then be able to reconstruct tracts. In that way, tracts descending from specific cortical areas or the cortico-spinal tracts should be possible to reconstruct. Considering baseline biomarkers computed as average over the whole brain or over entire WM tracts is also a way to bypass the difficulty of bringing infant and adult brain into a common anatomical space.

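### HP4.1 reads an infant–adult difference as an effect of brain age over the lifespan, but in this design age band coincides exactly with diagnosis and lesion timing, and nobody is enrolled between 18 months and 40 years

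*Protocol*

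**What the plan says.** HP4.1 expects remodelling of the damaged corticospinal tract (CST) in both populations after HABIT-ILE, and more of it in the infants. In the research hypotheses section of Grand Challenge 4, the protocol fixes the interpretation in advance. If the infants change more, the result is taken as confirmation that the immature brain is the more plastic one, and the sentence closes with the clause at issue: "especially when combined with intensive rehabilitation, allowing for a lifespan quantification of neuroplastic potential". If they do not, the result is said to challenge the classical view that the developing brain is more plastic. The discussion of HP4.3 reasons the same way: if no CST integrity threshold common to both populations can be found, that too is taken to point to different plasticity in developing and aged brains.

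The participants come from two trials:

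- Grand Challenge 2, Methods and Study Design: 48 infants, "being diagnosed or considered at high risk of unilateral (RCT1) cerebral palsy, 6 to 18 months inclusive".
- Grand Challenge 3, Clinical Study Design: 48 adults, "being 1) a hemiparetic patient with a chronic stroke (>6 months), 2) 40-90 years old"; "stroke of any type-size-location, involving either the dominant/non-dominant hemisphere will be included".

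The risk section expects drop-out or low intensity "both in infants and in adults who will mainly be up to 70 years of age", so the upper part of the adult range may be thinly filled. The title of Grand Challenge 4 describes its own contrast by lesion: very early against adult-acquired.

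**The concern.** The stated conclusion is about age, but the comparison behind it is between two clinical populations. They differ in age, and also in diagnosis and in when in life the lesion occurred. The protocol itself describes population-specific processes that could produce a difference in remodelling: persisting neuroinflammation (HP4.2) and preserved uncrossed CST axons after early damage (HP4.4). An infant–adult difference could come from any of these, from age, or from a mixture.

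Separately, a course over the lifespan needs observations across it. Two distant bands give one contrast and no information about the shape between them.

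What is at stake is the conclusion of HP4.1. Followed as written, the protocol would license a statement about brain age that its eligibility criteria cannot support. Its null-result sentence carries the same fault in the other direction.

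**Working it through.** The protocol gives no sample size, model or power for HP4.1, so there is no stated figure to reproduce. The check is whether the age effect can be identified.

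**1. Age coverage.** Lower and upper limits are 0.5 to 1.5 years (infants) and 40 to 90 years (adults).
- Span: 90 − 0.5 = 89.5 years.
- Gap: 40 − 1.5 = 38.5 years, and 38.5 / 89.5 = 43% of the span.
- Planned participants in the gap: 0 of 48 + 48 = 96.

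**2. Age band against lesion population.**

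| | CP, very early lesion | Chronic stroke, adult-acquired lesion |
|---|---|---|
| 6–18 months | 48 | 0 |
| 40–90 years | 0 | 48 |

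Both off-diagonal cells are empty by design. With an intercept, an age-band indicator and a lesion-population indicator, the last two columns are identical, so the design matrix has rank 2 with 3 columns. Only the sum of the two effects can be estimated. Subtracting each trial's own control group may remove maturation or spontaneous change, but it leaves this table unchanged.

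**3. Continuous age instead of bands.** Assume ages uniform within each band.
- Means are 1 and 65 years, so the between-population variance is (64 / 2)² = 1024.
- Within-population variances are 1² / 12 = 0.083 and 50² / 12 = 208.3, averaging 104.2.
- The squared correlation of age with population is 1024 / (1024 + 104.2) = 0.908, so |r| is about 0.95 and the variance inflation factor is 1 / (1 − 0.908), between 10 and 11.

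The matrix now has full rank, but only by assuming one straight line in age across both populations. Almost all the within-band information comes from the adults: 208.3 / (208.3 + 0.083) is above 99.9%. The age term would in effect be the adult slope, carried back across 38.5 empty years.

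**4. What can be estimated within each trial.** For an arm-by-age interaction with n per arm and residual SD σ, the standard error of the slope difference is σ × √(2/n) / SD(age). The 95% half-width is 1.96 times that.

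- Infants, n = 24, SD(age) = 12 / √12 = 3.46 months: standard error 0.289 / 3.46 = 0.083σ per month; half-width 1.96 × 6 × 0.083 = 0.98σ per 6 months.
- Infants, n = 17 (about 70% of 24, the minimum MRI success rate given in the risk section): √(2/17) = 0.343; standard error 0.099σ per month; half-width 1.16σ per 6 months.
- Adults, n = 24, uniform over 40–90, SD(age) = 50 / √12 = 14.4 years: standard error 0.020σ per year; half-width 0.78σ per 20 years.
- Adults, n = 24, uniform over 40–70, SD(age) = 30 / √12 = 8.66 years: standard error 0.033σ per year; half-width 1.31σ per 20 years.

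These estimates do not carry the between-band confounding, but they are wide and do not answer the infant-versus-adult question.

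**The case against.** The strongest defence is that HP4.1 is already worded as a comparison of infants with CP and adults with stroke, and that only a trailing clause goes further. The step is called exploratory, the key sentence is hedged with *potentially*, and no sample size, endpoint or allocation depends on it. The introduction to Grand Challenge 4 attributes differential repair to initial conditions and age together, so the protocol does not credit age alone throughout. All of this is fair and limits the weight of the point. It does not rescue the clause: calling an analysis exploratory does not make an aliased effect identifiable, and the text still says what the result would confirm.

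A reader might infer more than the documents support:

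- *That no age effect can be studied at all.* This is not so. The loss of identifiability applies between the bands. Age within infancy or within 40–90 years can be examined, and HP2.4 already asks about onset of therapy within infancy.
- *That the two groups have different lesion types.* The protocol does not list infant aetiologies and admits stroke of any type. What it establishes is a different diagnosis and different lesion timing, which is enough for the confounding.
- *That an age curve, or estimates at unobserved ages, will be reported.* The protocol promises neither. The documented fault is the conclusion it states in advance.

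The project plan (WP3) also lists existing and public diffusion MRI databases. These might bridge ages, but they are given no role in HP4.1.

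**Conclusion.** The point holds in a limited form. The infant–adult difference in HP4.1 cannot be attributed to age, because age band coincides exactly with diagnosis and lesion timing. Nor can it describe a lifespan course, because 43% of the age span contains no participants. Both statements follow from the eligibility criteria alone and need no distributional assumption. Because the cause is who is enrolled, a later choice of analysis model within these two trials cannot repair it.

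The correlation, the inflation factor and the half-widths rest on assumed uniform ages within each band. The half-widths also assume full retention, except in the 17-per-arm infant case.

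The fault is an overstated inference in an exploratory aim. It leaves both randomised comparisons untouched, so it is a minor point, though as written it leads to an unsupported conclusion.

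**What to change.** In the HP4.1 paragraph, delete the clause on lifespan quantification. State the conclusion, whether or not the hypothesis is verified, as an exploratory contrast between infants with unilateral CP and adults with chronic stroke, who differ in both age and lesion. Make the same change to the sentence under HP4.3 that reads the absence of a common CST threshold as evidence about developing and aged brains.

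If the investigators want to say something about age, they may report an arm-by-age estimate within each trial with its confidence interval, labelled exploratory. This is optional and, on the half-widths above, likely to be very imprecise.

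The cost is wording only: no new data, no extra participants and no change to any procedure. The downside is a less ambitious claim.
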